**5 Treatment**

The combination of SBRT with sintilimab and GM-CSF is applied. One lesion (primary or metastatic lesion) is selected for SBRT, with the dose of 24Gy/3Fx. Within Two weeks after SBRT is completed, Sintilimab and GM-CSF treatment are initiated and used in combination, with the date recorded as d1. GM-CSF is continuously used for 14 days (d1-d14) at the dose of 125 μg/m^2^. Sintilimab is administrated at the dose of 200 mg/time once every 3 weeks from d1 (d21n +1, n≥0), 35 cycles in total (2 years), or until the investigator deems that the patient needs to be discontinued due to treatment-related toxicity or disease progression. The overall response rate and toxicity were assessed periodically.

**5.1 SBRT**

One primary or metastatic lesion with a size of 1-5 cm, a clear boundary, little influence on surrounding normal tissues and no previous irradiation is selected and performed SBRT. The total dose of each lesion is 24 Gy/3 Fx (8 Gy/Fx). Each lesion is irradiated once a day for 3 consecutive days. Taking into account the failure of the radiotherapy machine and other factors, it is allowed to complete 3 fractions within 5 days.

**The principle of lesion selection:**

1. Try to choose lesions with less damage to normal tissues.
2. Try to choose the largest one among all the available lesions, but the size should not exceed 5cm.
3. For bone metastases, if there is no obvious soft tissue mass, they should not be selected for SBRT.
4. Brain metastases should not be selected for SBRT treatment.
5. The lesions that are easier to undergo biopsy should be kept for biopsy, and not be selected for SBRT.

**5.1.1 Positioning and Simulation**

Equipment: Analog CT

Scanning range: The target area and all organs at risk should be covered. The scanning length is extended by at least 5-10cm to the cephalic and crural sides of the boundary of the target area.

Scanning layer thickness: 3 mm/layer.

Contrast agent application: If appropriate.

**5.1.2 Definition of target volume**

**GTV:** The visible tumor displayed during CT simulation. MRI, PET and other information should be referred to for the evaluation of tumor size and extent when necessary.

CTV: In this study, CTV=GTV

ITV: Respiratory motion control technology is required for lesions that are significantly affected by respiratory motion. 4DCT technology is strongly recommended, the respiratory motion control methods of which include chest/abdominal compression, active respiratory control technology (ABC), and respiratory gating technology.

**PTV:** Cone-beam CT (cone-beam CT) must be performed to verify the body position before each SBRT treatment, so the external placement boundary from ITV to PTV is 5mm.

**5.1.3 Radiation dose**

The prescribed dose of PTV is 24 Gy/3Fx. Tumor prescription dose requirements include that the dose is normalized to the average dose point of PTV, that 95% PTV receives the prescribed dose, that 99% PTV receives 95% of the prescribed dose, and that the area < 95% of the prescribed dose cannot fall on the GTV.

**5.1.4 Dose constrains for organ at risk (according to AAPM Task Group 101 document)**

**Table 2. Dose constrains for OAR**

| **Tandem organs** | **Volume** | **Maximum volume dose (Gy)** | **Maximum point dose (Gy)** | **Adverse events (≥ grade 3)** |
| --- | --- | --- | --- | --- |
| Visual pathway | <0.2cc | 15.3Gy | 17.4Gy(5.8Gy/Fx) | Neuritis |
| Cochlea |  |  | 17.1Gy(5.7Gy/Fx) | Hearing loss |
| Brainstem (not spinal cord) | <0.5cc | 18Gy(6Gy/Fx) | 23.1Gy(7.7Gy/Fx) | Cranial neuropathy |
| Vertebral body  spinal cord | <0.35cc  <1.2cc | 18Gy(6Gy/Fx)  12.3Gy(4.1Gy/Fx) | 21.9Gy(7.3Gy/Fx) | Myelitis |
| Spinal cord segmentation (upper and lower 5-6 mm each) | <10% segment volume | 18Gy(6Gy/Fx) | 21.9Gy(7.3Gy/Fx) | Myelitis |
| Horsetail | <5cc | 21.9Gy(7.3Gy/Fx) | 24Gy(8Gy/Fx) | Neuritis |
| Sacral plexus | <5cc | 22.5Gy(7.5Gy/Fx) | 24Gy(8Gy/Fx) | Neuropathy |
| Esophagus | <5cc | 17.7Gy(5.9Gy/Fx) | 25.2Gy(8.4Gy/Fx) | Stenosis/fistula |
| Brachial plexus | <3cc | 20.4Gy(7.5Gy/Fx) | 24Gy(8Gy/Fx) | Neuropathy |
| Heart/pericardium | <15cc | 24Gy(8Gy/Fx) | 30Gy(10Gy/Fx) | Pericarditis |
| Great blood vessels | <10cc | 39Gy(13Gy/Fx) | 45Gy(15Gy/Fx) | Aneurysm |
| Trachea and main bronchus | <4cc | 15Gy(5Gy/Fx) | 30Gy(10Gy/Fx) | Stenosis/fistula |
| Bronchial branches | <0.5cc | 18.9Gy(6.3Gy/Fx) | 23.1Gy(7.7Gy/Fx) | Stenosis with atelectasis |
| Ribs | <1cc  <1cc | 28.8Gy(9.6Gy/Fx)  30.0Gy(10.0Gy/Fx) | 36.9Gy(12.3Gy/Fx) | Pain or fracture |
| Skin | <10cc | 30Gy(10Gy/Fx) | 33Gy(11Gy/Fx) | Ulcer |
| Stomach | <10cc | 16.5Gy(5.5Gy/Fx) | 22.2Gy(7.4Gy/Fx) | Ulcer/fistula |
| Bile duct |  |  | 35.7Gy(11.9Gy/Fx) | narrow |
| Duodenum | <5cc  <10cc | 16.5Gy(5.5Gy/Fx)  11.4Gy(3.8Gy/Fx) | 22.2Gy(7.4Gy/Fx) | ulcer |
| Jejunum/ileum | <5cc | 17.7Gy(5.9Gy/Fx) | 25.2Gy(8.4Gy/Fx) | Inflammation/obstruction |
| Colon | <20cc | 24Gy(8Gy/Fx) | 28.2Gy(9.4Gy/Fx) | Colitis/Fistula |
| Rectum | <20cc | 24Gy(8Gy/Fx) | 28.2Gy(9.4Gy/Fx) | Proctitis/Fistula |
| Ureter |  |  | 48.9Gy(16.3Gy/Fx) | Narrow |
| Bladder wall | <15cc | 16.8Gy(5.6Gy/Fx) | 28.2Gy(9.4Gy/Fx) | Cystitis/Fistula |
| Vaginal sperm | <3cc | 21.9Gy(7.3Gy/Fx) | 42Gy(14Gy/Fx) | Impotence |
| Femoral head (left/right) | <10cc | 21.9Gy(7.3Gy/Fx) |  | Necrosis |
| Renal Hilar/Main Vessel | <2/3 volume | 18.6Gy(6.2Gy/Fx) |  | Malignant hypertension |
| **Parallel organs** | **Critical volume** | **Maximum critical volume dose (Gy)** |  | **Adverse events (≥ grade 3)** |
| Lung (left/right) | 1500cc | 11.6Gy(2.9Gy/Fx) |  | Basic lung function |
| Lung (left/right) | 1000cc | 12.4Gy(3.1Gy/Fx) |  | Pneumonia |
| liver | 700cc | 19.2Gy(4.8Gy/Fx) |  | Basic liver function |
| Renal cortex (left/right) | 200cc | 16.0Gy(4.0y/Fx) |  | Basic kidney function |

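### Five organ-at-risk entries in Protocol Table 2 contradict the three-fraction regimen: both lung rows, liver and renal cortex imply four fractions, and the brachial plexus volume limit implies 2.72

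*Protocol*

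**What the plan says.** The fractionation is fixed. Section 5.1 states "The total dose of each lesion is 24 Gy/3 Fx (8 Gy/Fx", and section 5.1.3 repeats it: "The prescribed dose of PTV is 24 Gy/3Fx". Section 5.1 allows up to five days in case of machine failure, but still for three fractions.

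Table 2 in section 5.1.4 sets the normal-tissue limits, which its heading attributes to a task-group report (reference 26). Most entries print a total dose with a per-fraction dose in brackets. The entries at issue are:

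- Lung, 1500 cc: "11.6Gy(2.9Gy/Fx"
- Lung, 1000 cc: "12.4Gy(3.1Gy/Fx"
- Liver, 700 cc: "19.2Gy(4.8Gy/Fx"
- Renal cortex, 200 cc: "16.0Gy(4.0y/Fx" (read here as 4.0 Gy per fraction)
- Brachial plexus, under 3 cc: "20.4Gy(7.5Gy/Fx"

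For comparison, the sacral plexus row has the same per-fraction dose as the brachial plexus row, with a different total: "22.5Gy(7.5Gy/Fx". No footnote or text gives a different number of fractions for any row, or says whether the total or the bracketed figure governs.

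**The concern.** With three fractions, each total should be three times its per-fraction dose. Where it is not, the row states two different limits for the same organ, and a planner cannot meet both as equivalent constraints.

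The mismatch covers every row of the parallel-organ block, always with a ratio of 4. That pattern suggests figures taken, in whole or in part, from a four-fraction schedule. The column headings name a dose in Gy, so a planner would naturally apply the total, and in these four rows the total is the more lenient figure.

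The lung rows matter most. This is a lung cancer trial in which the irradiated lesion may be the primary. Table 2 links the 1000 cc lung limit to pneumonia of grade 3 or worse, and section 5.2.2 makes grade 3-4 pneumonitis a reason to stop sintilimab permanently. The study is multi-center, so centres could also resolve the ambiguity differently.

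**Working it through.** **Inputs.** The number of fractions is 3 (sections 5.1 and 5.1.3; 3 × 8 = 24 Gy). The totals *T* and per-fraction doses *d* come from Table 2.

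**Formulas.** The implied number of fractions is *T* / *d*, which should be 3. If *d* is right, the total should be 3 × *d*. If *T* is right, the per-fraction dose should be *T* / 3. The gap is *T* / (3 × *d*) − 1.

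**All entries.** Table 2 has 53 entries with both figures: 49 in the serial-organ block (headed tandem organs) and 4 in the parallel-organ block. The visual pathway volume limit of 15.3 Gy has no per-fraction dose and cannot be tested. In 48 of the 49 serial-organ entries *T* / *d* is exactly 3.00, for example 22.5 / 7.5 for the sacral plexus and 24 / 8 for the brachial plexus point dose. So the table's convention is clear, and rounding does not explain the exceptions.

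**The five exceptions.**

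| Entry | *T* (Gy) | *d* (Gy) | *T* / *d* | 3 × *d* (Gy) | *T* / 3 (Gy) | Gap |
|---|---|---|---|---|---|---|
| Lung 1500 cc | 11.6 | 2.9 | 4.00 | 8.7 | 3.87 | +33.3% |
| Lung 1000 cc | 12.4 | 3.1 | 4.00 | 9.3 | 4.13 | +33.3% |
| Liver 700 cc | 19.2 | 4.8 | 4.00 | 14.4 | 6.40 | +33.3% |
| Renal cortex 200 cc | 16.0 | 4.0 | 4.00 | 12.0 | 5.33 | +33.3% |
| Brachial plexus <3 cc | 20.4 | 7.5 | 2.72 | 22.5 | 6.80 | −9.3% |

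**Reading the four parallel-organ rows.** If *d* is right, each total must fall by 25% (for example 8.7 / 11.6 = 0.75). The reductions are 2.9, 3.1, 4.8 and 4.0 Gy. If *T* is right, the limits stand and only the bracketed figures change, to 3.87, 4.13, 6.40 and 5.33 Gy.

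**Reading the brachial plexus row.** The total is below 3 × *d*, so applying it errs on the safe side. A total of 20.4 Gy needs 6.8 Gy per fraction. The printed 7.5 Gy equals the sacral plexus figure, so it may have been carried over from that row.

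**The case against.** The strongest reply is that no governing limit has been shown to be wrong. The column headings point to the total, and the bracket can be read as an annotation. If the totals are the correct three-fraction values, only five bracketed numbers are wrong and every plan stands. Whether the totals are too lenient depends on the cited report, which is not at hand, and sites could consult it themselves. The clinical effect is also unproven: one lesion of 1 to 5 cm is treated, chosen to spare normal tissue, and section 5.1.5 calls for an overall review of dose-volume histograms and isodose displays. These limits may seldom bind. The brachial plexus total is the stricter figure, so that row adds no demonstrated risk.

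Much of this stands. The documents cannot settle which figure is right, the 33% gap is a safety issue only if the per-fraction figures are the correct ones, and the brachial plexus entry may be a simple copying slip. But the reply does not remove the contradiction. The protocol prints both figures without saying which governs, and planners would normally work from the printed table. Extraction damage is an unlikely cause, since four adjacent rows all give exactly 4. General planning safeguards do not replace correct limits.

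**Conclusion.** The point holds and should be fixed. Five of 53 testable entries contradict the three-fraction regimen: four by a factor of exactly 4/3, and one by −9.3%. The arithmetic rests only on the printed figures and on reading the renal cortex unit as Gy.

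The consequence is conditional. If the four parallel-organ totals come from a four-fraction schedule, the printed limits may be too lenient for this trial; if the totals are right, the error is confined to the brackets. The documents do not decide between these. The sample size and the ORR analysis are unaffected, and no effect on the dose-limiting toxicity count is shown.

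**What to change.** Check the five entries against the three-fraction limits in the task-group report cited in section 5.1.4. Reissue Table 2 with one total and a matching per-fraction dose in each row. For the brachial plexus, check whether 7.5 Gy per fraction was copied from the sacral plexus row; if the 20.4 Gy total is right, the bracket should read 6.8 Gy.

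At the same time, check the rib row, which lists a volume under 1 cc twice, at 28.8 and 30.0 Gy. Both fit three fractions (28.8 / 9.6 = 3 and 30.0 / 10.0 = 3), so the second limit is redundant rather than contradictory, but a volume or dose may have been mis-entered.

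The cost is the correction of five table entries, plus a re-check of approved plans only for rows whose total becomes stricter.

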**5.1.5 Radiotherapy plan**

The linear accelerator is used, which is 6MV X-rays, and the width of MLC is ≤ 5mm. The radiation field is designed with a fixed field and/or a dynamic rotating field. Pulmonary heterogeneity correction was performed when calculating the dose. The shape of the irradiation field is designed by Beams Eye View (BEV). An isotropic grid system less than or equal to 2 mm is used when calculating the volume. The treatment plan is determined by comprehensive evaluation of Dose Volume Histogram (DVH), isodose line graphs, two-dimensional isodose line and Color washing.

**5.1.6 Implementation and verification of radiotherapy plan**

Cone-beam CT must be performed to verify the body position, and the placement error must be corrected before each SBRT.

**5.2 Sintilimab**

Starting on the second day (d1) after the completion of SBRT treatment, Sintilimab was given intravenously once every 3 weeks at a dose of 200 mg. Blood routine, blood biochemistry, coagulation function, and thyroid function should be checked before each administration, in order to evaluate the related adverse events. During each 3 courses of treatment (every 9 weeks), the efficacy is evaluated (according to the RECIST1.1), and the treatment is continued until disease progression, death, unacceptable toxicity or up to 35 cycles (2 years) or the patient withdraws informed consent. See 5.2.1-5.2.8 for the principles of Sintilimab use, withdrawal, resumption of medication, infusion reaction management, dose adjustment, toxicity management, concomitant treatment and drug management.

**5.2.1 Use of Sintilimab**

The main active ingredient of IBI308 is a recombinant fully humanized anti-programmed death receptor 1 monoclonal antibody with a concentration of 10 mg/mL. This product is a clear, colorless liquid, free of foreign matter, flocculation and precipitation. Excipients include 140 mmol/L mannitol, 25 mmol/L histidine, 20 mmol/L sodium citrate dihydrate, 50 mmol/L sodium chloride, 0.02 mmol/L disodium edetate (ethylenediamine tetra Disodium acetate), 0.2 mg/mL polysorbate 80, pH 6.0.

The smallest packaging unit of IBI308 is a box, and each box contains 1 Sintilimab injection packaged in a vial. The packaging box is printed with the name of the drug, dosage form, specification, drug code, production batch number, expiration date, storage conditions and information of the sponsor. The same information is printed on the label of the vial and the box, but there is no information on the dosage form, precautions, usage and dosage on the label of the vial. The labels of all packaging boxes and vials are marked "For clinical research use only". Sintilimab products are stored in the dark at 2~8℃, and the validity period is 24 months. If there are quality problems such as turbidity and precipitation in the injection, it should be sealed up immediately, and Innovent Biologics (Suzhou) Co., Ltd. (hereinafter referred to as "Innovent Biologics") should be notified immediately.

The preparation and infusion process of IBI308 is as follows:

1. Draw out 2 bottles of IBI308 injection completely, add 100mL 0.9% (weight/volume) sodium chloride sterile saline intravenous infusion bag, and record the start time of preparation.

2. Gently invert the infusion bag to mix to ensure the uniformity of the medicine in the infusion bag and avoid foaming due to violent shaking. If a large amount of foam is generated, the drug should be allowed to stand until the foam disappears.

3. The drug is administered through a filter equipped with 0.2~1.2μm (it is recommended that the infusion time be controlled within 30-60 minutes), and the start time and end time of the drug delivery are recorded.

Note: Before configuration, confirm that the IBI308 injection is transparent, and there are no quality problems such as turbidity or precipitation; ensure that the time from the first bottle of IBI308 injection to the end of administration does not exceed 24 hours (the storage condition of the prepared drug is kept in a refrigerator refrigerated at 2~8℃); avoid mixing other drugs; avoid intravenous bolus injection.

**5.2.2 Principles of Suspension and Permanent Discontinuation of Sintilimab**

The dose of Sintilimab is not allowed to be adjusted during the entire study. The principles of suspension and permanent discontinuation of Sintilimab are shown in the table below.

| **Adverse events related to Sintilimab** | **Severity** | **Dose adjustment** |
| --- | --- | --- |
| Pneumonitis | Grade 2 | Suspend dosing ^a^ |
|  | Recurrent grade 2 or grade 3-4 | Permanent discontinuation |
| Diarrhea/Enterocolitis | Grade 2 or 3 | Suspend dosing ^a^ |
|  | Grade 4 | Permanent discontinuation |
| Dermatitis | Grade 3 | Suspend dosing ^a^ |
|  | Grade 4 | Permanent discontinuation |
| Hepatitis | For subjects with normal baseline ALT, AST, or TBIL, Grade 2 elevation in AST, ALT, or TBIL;  For subjects with baseline AST, ALT, or TBIL>ULN, elevation in AST, ALT or TBIL ≥50% and duration<7 days | Suspend dosing ^a^ |
|  | For subjects with normal baseline ALT, AST, or TBIL, Grade3-4 elevation in AST, ALT, or TBIL; For subjects with baseline AST, ALT, or TBIL>ULN, AST, ALT, or TBIL increased by ≥50% and the duration ≥ 7 days | Permanent discontinuation |
| Hypophysitis | Grade 2 | Withhold dosing ^b^ |
|  | Grade 3 or 4 | Permanent discontinuation |
| Adrenal insufficiency | Grade 2 | Suspend dosing ^b^ |
|  | Grade 3 or 4 | Permanent discontinuation |
| Hyperthyroidism | Grade 3 or 4 | Permanent discontinuation |
| Type I diabetes | Grade 3 | Suspend dosing ^b^ |
|  | Grade 4 | Permanent discontinuation |
| Renal insufficiency | Grade 2 or 3 | Suspend dosing ^b^ |
|  | Grade 4 | Permanent discontinuation |
| Neurotoxicity | Grade 2 | Suspend dosing ^a^ |
| Neurotoxicity | Grade 3 or 4 | Permanent discontinuation |
| Other AE | First appearance Grade 3 | Suspend dosing ^a^ |
|  | Second occurrence Grade 3 | Permanent discontinuation |
|  | Cannot drop to grade 0-2/baseline level within 7 days or return to grade 0-1 within 14 days/Baseline level 3 AE | Permanent discontinuation |
|  | Grade 4 AE | Permanent withdrawal ^c^ |

**Table 3. Suspension and permanent withdrawal of Sintilimab**

a: Resume administration after the symptoms improved to grade 0-1 or baseline level.

b: For hypophysitis, adrenal insufficiency, thyroid insufficiency/hypothyroidism, and type 1 diabetes, Sintilimab can be restarted if they are fully controlled and require only physiological hormone replacement therapy.

c: For abnormal grade 4 laboratory test results, the decision to terminate the medication should be based on the accompanying clinical symptoms/signs and the clinical judgment of the investigator.

The maximum interval allowed for drug suspension is 12 weeks. If it is not possible to return to the state where Sintilimab can be re-used within 12 weeks, the subject will permanently stop Sintilimab and enter the follow-up phase. Except for the following two cases:

1. Due to the application of glucocorticoids in the treatment of irAE, the process of glucocorticoid reduction led to the suspension of Sintilimab for more than 12 weeks. In this case, it is necessary to discuss with the sponsor's medical manager to decide whether to continue Sintilimab treatment. The imaging examination to evaluate the efficacy is carried out as planned, and is not affected by the suspension of medication.

2. Sintilimab was suspended for more than 12 weeks due to treatment related AEs unrelated to Sintilimab. In this case, it is necessary to discuss with the sponsor to decide whether to continue Sintilimab treatment. The imaging examination to evaluate the efficacy is carried out as planned, and is not affected by the suspension of medication.

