**5.2.3 Restoration of Sintilimab**

Resuming use of Sintilimab requires that treatment related AEs to return to grade 0-1 or baseline, with an ECOG PS score of 0-1.

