**7.3 Assessment of adverse events**

The investigator will evaluate all adverse events in accordance with NCI Common Adverse Events (CTCAE) version 5.0. Any adverse event that changes the CTCAE level will be recorded in the adverse event case report form/worksheet. All adverse events, regardless of the CTCAE grade, must be evaluated whether they are serious adverse events. For specific details, please refer to the table below.

Adverse event assessment rules

| **CTCAE**  **Grade** | **Level 1** | **Mild; asymptomatic or mild; only clinical or diagnostic manifestations; no intervention required** |
| --- | --- | --- |
|  | **Level 2** | **Moderate; requires minimal, partial or non-invasive intervention; restricts daily activities of the appropriate age** |
|  | **Level 3** | **Severe or important medical events require medication, but they are not immediately life-threatening; hospitalization or extended hospitalization; disability; limitation of self-care ability ADL** |
|  | **Level 4** | **Life-threatening consequences; urgent intervention required** |
|  | **Level 5** | **AE-related deaths** |
| **Severity** | A serious adverse event is any of the following adverse events that occur at any dose or during any use of the study drug: | |
|  | †Causes **death;** | |
|  | †Life **threatening; or** in the eyes of the researcher, the occurrence of the event puts the subject at immediate risk of death (Note: This does not include adverse events that may lead to death if they occur in a more serious form); | |
|  | †Causes **permanent or severe disability/dysfunction; (seriously interferes with the** ability to carry on a normal life); | |
|  | †Causes **or prolongs existing hospitalization; (Hospitalization** is defined as a hospitalization, regardless of the length of hospitalization, even if the hospitalization is only a preventive measure for continued observation. Note: Hospitalization [including hospitalization due to elective surgery] due to an existing disease that did not worsen during the study period does not constitute a serious adverse event. Pre-existing diseases refer to clinical diseases that were diagnosed before the use of study drugs and recorded in the patient's medical history); | |
|  | †Congenital **abnormalities/birth defects; (the offspring of** subjects who use the product, regardless of the time of diagnosis); | |

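### The sintilimab restart rule for endocrine toxicity in Table 3 footnote b is not reconciled with section 5.2.3, and the renal insufficiency row carries a footnote that cannot apply to it

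*Protocol*

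**What the plan says.** Table 3 (protocol section 5.2.2) lists when sintilimab is suspended and when it is stopped for good. Most suspension entries carry footnote a, under which dosing resumes once symptoms are back to grade 0-1 or baseline. Four entries carry footnote b:

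- hypophysitis, grade 2;
- adrenal insufficiency: "Adrenal insufficiency | Grade 2 | Suspend dosing ^b";
- type 1 diabetes: "Type I diabetes | Grade 3 | Suspend dosing ^b";
- renal insufficiency: "Renal insufficiency | Grade 2 or 3 | Suspend dosing ^b".

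Footnote b opens with the conditions it covers, "b: For hypophysitis, adrenal insufficiency, thyroid insufficiency/hypothyroidism, and type 1 diabetes", and then gives its rule: "Sintilimab can be restarted if they are fully controlled and require only physiological hormone replacement therapy".

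Section 5.2.3 is the section on resuming the drug. It says: "Resuming use of Sintilimab requires that treatment related AEs to return to grade 0-1 or baseline", and adds an ECOG score of 0-1.

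The text under Table 3 limits a suspension to 12 weeks. "If it is not possible to return to the state where Sintilimab can be re-used within 12 weeks", the drug is stopped permanently. There are two exceptions, both to be discussed with the sponsor: a suspension prolonged by tapering glucocorticoids given for an immune-related event, and a suspension for a treatment-related event not due to sintilimab.

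The general grading table in section 7.3 describes level 1 as: "Mild; asymptomatic or mild; only clinical or diagnostic manifestations; no intervention required". Level 2 is described as needing some intervention.

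**The concern.** Footnote b and section 5.2.3 set different tests for the same decision. The footnote asks whether the condition is controlled on replacement hormone. Section 5.2.3 asks what grade the event has reached. A patient can pass one test and fail the other, and the protocol does not say which passage governs.

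The renal row has a different fault. It sends the reader to a footnote written for endocrine events, so the table gives no usable restart criterion for that toxicity.

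At stake are patient safety and uniform treatment across the sites of a multi-centre study. Sintilimab may run to 35 cycles, so whether a suspension ends in a restart or a permanent stop matters a good deal to the patient concerned. An unclear rule also makes it harder to judge whether a given restart was a protocol deviation.

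**Working it through.** No arithmetic applies, so the check sets the passages side by side.

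**Endocrine events**

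| Question | Table 3 footnote b | Section 5.2.3 |
| --- | --- | --- |
| Which events? | Four named endocrine conditions | All treatment-related events |
| Condition on the event | Controlled, with only physiological replacement needed | Grade 0-1 or baseline |
| Grade condition? | None | Yes |
| ECOG condition? | None | 0-1 |
| Refers to the other passage? | No | No |

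1. Take a patient suspended for grade 2 adrenal insufficiency who then becomes stable on continuing replacement, with ECOG 0-1. Footnote b allows the restart.
2. Apply 5.2.3 to the same patient. By the general descriptors in 7.3, level 1 needs no intervention and level 2 does. Replacement is an intervention, so the patient is arguably still above grade 1.
3. The baseline alternative does not help if the condition arose on treatment, because the patient did not have it at entry. Read literally, 5.2.3 is not met.
4. Apply the 12-week limit. It turns on whether the patient has reached a state in which the drug may be used again, and it does not define that state. Under footnote b the state is reached. Under 5.2.3 it is not, and the stop becomes permanent unless one of the two exceptions applies. The permanent stop therefore needs 5.2.3 and the 12-week limit together.
5. Neither exception is written for continuing replacement as such. The glucocorticoid-taper exception could still cover some immune-related endocrine events.

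The same reasoning applies to hypophysitis grade 2 and type 1 diabetes grade 3, which makes three rows.

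**Renal insufficiency**

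1. Grade 2 or 3 is marked b.
2. Footnote b does not name renal insufficiency, and its hormone-replacement condition has no meaning for it.
3. What remains is 5.2.3: grade 0-1 or baseline, with ECOG 0-1. A rule exists, but the table does not point to it.

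**Hypothyroidism**

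Footnote b names it, but Table 3 has no row for it, so no entry leads the reader from hypothyroidism to the footnote. The only thyroid row is hyperthyroidism grade 3 or 4, which is a permanent stop and needs no restart rule.

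**The case against.** The strongest reply is that footnote b is a specific rule attached to specific rows, while 5.2.3 is a general rule that repeats footnote a and adds ECOG. If 5.2.3 overrode footnote b, the footnote would do nothing for patients still on replacement, the group it seems written for. Reading it as an exception gives both passages effect. This is a sensible reading and may be what was intended. It does not remove the point: 5.2.3 is worded as a requirement, neither passage mentions the other, and sites should not have to infer precedence on a safety rule. It does mean that one cannot say sites will in fact treat identical patients differently. A reader might infer that, but the protocol shows only that its wording allows it.

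The second reply is that the conflict rests on a grading inference. The protocol grades events by CTCAE 5.0, and its event-specific criteria are not reproduced. The descriptors in 7.3 are generic. This stands, and is why the patient on replacement is described only as arguably above grade 1.

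The third reply is that section 5.2.6 refers sites to a sponsor manual on immune-related events, which may settle the matter. The manual is not at hand, and 5.2.6 does not say that it overrides 5.2.2 or 5.2.3. Whether it reconciles them cannot be judged here.

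**Conclusion.** The restart rules as written are inconsistent for the three endocrine rows marked b, and the renal row carries a footnote that does not fit it. The endocrine conclusion rests on two assumptions: that a patient on continuing replacement is above grade 1, which the general descriptors in 7.3 support but do not settle, and that 5.2.3 is read literally. A permanent stop needs the 12-week limit as well, and holds only if neither exception applies.

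Three stronger readings are tempting but not supported:

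- **Renal patients face a choice between restart and permanent stop.** They do not. Footnote b says nothing about them and 5.2.3 supplies a rule, so the fault is a wrong reference and not two conflicting outcomes.
- **The thyroid entries in table and footnote ought to match.** Hyperthyroidism and hypothyroidism are different conditions, and the protocol does not show that either entry is a mistake. The mention of hypothyroidism without a row is a matter for the sponsor to confirm.
- **ORR or PFS is distorted.** The protocol gives no rate for these toxicities, so the number of affected patients cannot be estimated. ORR is based on best response, and in both exceptions to the 12-week limit imaging stays on schedule. No route to a material effect is shown.

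The point is therefore one of clear and consistent safety instructions. It is worth correcting because the change is small and the decision matters to each patient it touches.

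**What to change.** Reconcile footnote b with section 5.2.3 so that each toxicity has one restart rule and the text says which passage takes precedence. This can be done by having 5.2.3 refer to footnote b as an exception, or by aligning the footnote with 5.2.3. State whether the ECOG condition applies in either case. Make the 12-week limit refer to the same rule, so that the state it relies on is defined.

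Correct the footnote reference on the renal insufficiency row so that it leads to a criterion that can apply to that event. Ask the sponsor's medical team to confirm whether the mention of hypothyroidism in footnote b is intended, given that Table 3 has no row for it. Check that the sponsor's manual on immune-related events agrees with the reconciled text.

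Which restart criterion applies is for the sponsor's medical team to decide. The cost is a short amendment or clarification letter to sites, with no added visits or data.
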